## Abstract

**Background:**

Rhinitis is a condition characterized by inflammation of the nasal mucosa. It causes obstruction and congestion in the nasal cavity. Clinically, it resembles *pratishyaya* (rhinitis) in Ayurveda, which is caused by accumulation and downward movement of the *tridoshas* (3 elements, named *vata*, *pitta*, and *kapha*) in the nasal cavity. Rhinitis is one of the most common diseases among children. There is no role for antibiotics in rhinitis, and nasal decongestants have also not been found to be effective in its management. In Ayurveda, *dhoopana* (nasal fumigation) is mentioned in the *pratishyaya* treatment protocol. However, we have found no previous study regarding its efficacy. The efficacy of *tulsi*, *vasa*, *nirgundi*, and *nilgiri* is already proven when they are used for steam inhalation in respiratory tract infections. Therefore, in this study, a *dhoopana* of a polyherbal formulation containing *tulsi*, *vasa*, *nirgundi*, and *nilgiri* will be compared with the inhalation of steam containing *arka* (a liquid obtained by distillation) of *tulsi*, *vasa*, *nirgundi*, and *nilgiri* leaves in children with *pratishyaya.*

**Objective:**

We aim to evaluate the efficacy of polyherbal steam inhalation as a standard control against *dhoopana* in children aged 7 to 14 years with *pratishyaya*.

**Methods:**

A total of 70 participants fulfilling the inclusion criteria were selected and distributed into 2 groups of 35 each. The intervention group received *dhoopana* and the control group received polyherbal steam inhalation, both twice daily for 7 days. The primary outcome measure was the change in Total Nasal Symptom Score and a modified cold spatula test. At the same time, the association between *prakriti* (body constitution) and the prevalence of *pratishyaya* in children was analyzed as a secondary outcome. Assessments were performed on days 3, 5, and 7, with a follow-up time of 28 days. Appropriate descriptive and inferential statistics will be used for data analysis.

**Results:**

As of November 2024, we have completed our enrollment of 70 patients, with 35 patients in each group. Data analysis will be completed by February 2025, and we expect results to be published in March 2025.

**Conclusions:**

We anticipate that polyherbal nasal fumigation will be found to be equally as effective as polyherbal steam inhalation in the management of acute rhinitis in the pediatric population. This study may provide a standardized, herbal, safe, and cost-effective treatment for rhinitis in children in the form of *dhoopana*.

**International Registered Report Identifier (IRRID):**

DERR1-10.2196/58197

## Introduction

### Overview

Rhinitis is defined as inflammation of the nasal mucosa due to any infection, allergy, or injury. Symptoms of rhinitis are sneezing, discharge from the nose, obstruction in the nasal cavity, irritation in the nasal cavity, body ache, a feverish sensation, and headache [1]. As per Ayurveda, a clinical picture of rhinitis is seen in the disease *pratishyaya*. It is one of the *nasagata roga* (nasal disorders) in which *kaphadi tridoshas* (the 3 elements of the body) are continuously eliminated through the nose. These vitiated *doshas* accumulate in the head, and their further movement toward the nose causes *pratishyaya* [2]. According to Acharya Charaka, the definition of *pratishyaya* is “*pratikshnam shyayatiitipratishyaya*,” which means the “continuous outward movement of *vata*, *pitta*, and *kapha* doshas from the nostrils.” The prevalence of nonallergic rhinitis is about 40% [3]. The prevalence of allergic rhinitis in India was reported as “11.3% in children aged 6-7 years and 24.4% in children aged 13-14 years” [4]. Acharya Videha explained the clinical presentation of *pratishyaya* as excessive secretions from the nasal cavity and eyes, fever, and generalized weakness with severe headache [2]. *Pratishyaya* is classified into 5 types: *vataja*, *pittaja*, *kaphaja*, *sannipataja*, and *raktaja pratishyaya* [2,5]. The nasal mucosa has a rich blood supply, and stimulation of the sympathetic nervous system causes vasoconstriction that results in shrinkage of the nasal mucosa on the other side, while stimulation of the parasympathetic nervous system is responsible for excessive secretion from the nasal mucosa along with dilatation of local vessels. Emotional disturbance also plays a significant role, as the autonomic nervous system innervation of the nasal mucosa is under the control of the hypothalamus [3]. If no treatment is given at an early stage, the condition may become complicated and lead to comorbid conditions like chronic rhinitis, cough, or breathing difficulty and debility [2]. There is no use of antibiotics in acute rhinitis [6]. Antihistamine decongestants are frequently used in cough and cold. However, in some studies, these were not found to be effective in the management of rhinitis [7]. There are limited data regarding the safety of pseudoephedrine and phenylephrine in rhinitis [8]. In Ayurveda, various oral medications are available for the management of this condition. However, it is difficult to administer Ayurvedic medicines orally to children. So, this study has been planned to find an effective way to manage the acute stage of rhinitis that can be administered locally in the nasal cavity. Various Ayurvedic interventions are mentioned in the Ayurveda classics as protocols for the management of *pratishyaya*, including *dhoopana* (nasal fumigation), an intervention that can effectively manage the disease. In this intervention, various herbs are made into a stick known as a *varti* (wick), and its fumes are used for local fumigation of the affected area. It can be considered an Ayurvedic therapy that delivers the medicines directly into the airways, providing relief and protection to the local region [9].

*Pratishyaya* treatment should be aimed at relieving the *avarodha* (obstruction) created by the dosha. Drugs having *ushna* (hot) and *tikshna* (pungent) properties are indicated in *dhoopana*. The efficacy of steam inhalation of *tulsi*, *vasa*, *nirgundi*, and *nilgiri* has already been shown in respiratory tract infections [10]. So, in this study, *dhoopana* of a polyherbal formulation containing *tulsi*, *vasa*, *nirgundi*, and *nilgiri* will be compared with a steam inhalation containing *arka* of *tulsi*, *vasa*, *nirgundi*, and *nilgiri* in *pratishyaya* in children. *Kashyapa Samhita* (an Ayurveda classical text) is mainly devoted to the Kaumarbhritya branch (Ayurvedic pediatrics) of Ashtanga Ayurveda, and *dhoopana* is described in the treatment protocol of *pratishyaya* [11]. There are many studies regarding the efficacy of oral medication in *pratishyaya* but there is no previous study available regarding the efficacy of local fumigation with medicated fumes in *pratishyaya* in children. Steam inhalation has a known soothing effect on the nasal mucosa in rhinitis. Herbal steam inhalation is more effective as compared to plain water steam inhalation [12], but steam inhalation is quite difficult to administer in children. So, in this study, we plan to compare the effect of polyherbal steam inhalation with polyherbal fumigation in children with *pratishyaya*. The herbs chosen for *dhoopana* were justified in previous studies, as steam inhalation of *tulsi*, *vasa*, *nirgundi*, and *nilgiri* was found to be effective for reducing local inflammation in the nostrils. A detailed description of previous articles and a research gap analysis with justification for this study is given in Table 1.

**Table 1 table1:** Previous studies and research gap analysis.

Reference	Conclusion	Remark
Memon [13]	*Vyoshadi vati* was found to be effective in reducing signs and symptoms of *pratishyaya* (rhinitis) in comparison with chlorpheniramine maleate in children aged 4-8 years.	Children tend to resist the intake of medicines orally in most cases, especially when they are sick. So, local fumes or steam inhalation could be a better choice.
Tarun and Anup [14]	*Nasya* with *tulasi swarasadi taila* and *haridrakhand* showed 100% results in objective as well as subjective parameters of *pratishyaya*. *Tulasi swarasadi taila nasya* and *haridrakhand* gave effective results in treating *pratishyaya*.	As *tulsi* has an anti-inflammatory effect and was found to be effective in the management of *pratishyaya*, and the *nasya* procedure is contraindicated in the acute stage, fume inhalation can be done with the use of *tulsi* in place of *nasya karma.* Local fume inhalation can provide instant relief for the symptoms of *pratishyaya*.
Rajput and Patni [15]	According to Acharya Charaka, any drug when instilled into the nostrils causes direct action in the brain; hence, it is highly effective in the treatment of various diseases related to the nervous system and supraclavicular region. The *nasya* procedure is indicated in *pratishyaya*. Standardization of *nasyakarma* with Ayurveda and modern scientific parameters with proper documentation is a current need.	*Nasya* is widely used in rhinitis but it is contraindicated in its acute stage. Moreover, it is quite difficult to administer to children. Direct contact with oil in the nostrils sometimes irritates children. In this study, acute cases were mentioned in the inclusion criteria, so local fumes could provide a better approach to the treatment of *pratishyaya*. Moreover, local nasal fumigation is described in the treatment protocol of *pratishyaya*, but no previous study has been done to determine its efficacy in rhinitis.
Kamble et al [16]	Steam inhalation of *tulsi* leaves was found to be more effective in reducing sign and symptoms of cough and cold in adults than steam inhalation of plain water.	*Tulsi* steam inhalation was found to be better than plain steam inhalation in the adult population. This shows that volatile herbs like *tulsi* have better efficacy when given locally in the form of vapors. Steam inhalation is also easier to administer in children. So in this study, *tulsi* was chosen as one of the herbs for fume as well as steam inhalation.

Sebastian and Sujatha [20]	The study showed that steam inhalation with *tulsi* leaves is effective in relieving symptoms of coryza compared to hot water steam inhalation in children aged 6-12 years.	The study was performed in a selected community with a small sample size, and no randomization was done. Steam inhalation was administered for only 3 days. The follow-up time was not mentioned in the article. This study is a randomized clinical trial, and *tulsi* along with *nilgiri*, *nirgundi* and *vasa* will be used for steam inhalation in the control group for 7 days with a follow-up of 28 days.
Macchi et al [21]	A statistically significant improvement was seen in ciliary motility in the first group, who received a nasal wash with sodium hyaluronate in saline solution (*P*<.001).	This was a pilot study with very small sample size. Moreover, the study included patients with recurrent upper respiratory tract infections; there was no specific disease chosen for the study. Aerosol use was indicated in lower respiratory tract infection, as there was a chance of the medicine entering the lungs. In our study, only *pratishyaya* cases will be included, rather than all patients with respiratory tract infections. Polyherbal fumes will be administered in the trial group, which could be a better alternative to aerosols.
Baartmans et al [22]	Annually, on average 3 people are admitted to a Dutch burn center for burns resulting from steam inhalation therapy. Most patients are children, and they need skin grafting more often than adults. At burn centers in the Netherlands, 31 patients were admitted with burns caused by steam inhalation therapy in the 1998 to 2007 period.	These data show that steam inhalation can result in burns, especially in children. So, in our study, we plan to find if *dhoopana* can be an alternative.
Murphy et al [23]	Between July 1 and December 31, 2002, 7 children were admitted to the burn unit of a children’s hospital in Dublin with scalds sustained during the course of steam inhalation. The children ranged in age from 9 months to 10 years. Techniques involving kettles or bowls of boiling water should be actively discouraged.	The common technique of steam inhalation is risky in children as it may cause burns. So, in our study, we plan to find an easier way to administer herbal effects to the nasal mucosa through *dhoopana*.

### Aim

We aim to study the efficacy of polyherbal steam inhalation versus *dhoopana* in children with *pratishyaya*.

### Primary Objectives

There are 3 primary objectives: first, to determine the efficacy of *dhoopana* in reducing signs and symptoms of *pratishyaya* compared to polyherbal steam inhalation; second, to study the duration of alleviation of Total Nasal Symptom Score (TNSS); and third, to determine the efficacy of *dhoopana* in the reduction of nasal obstruction in a modified cold spatula test.

### Secondary Objectives

There are 2 secondary objectives: first, to study the prevalence of *pratishyaya*, its origin, and its causative factors, such as viruses, bacteria, or allergies; second, to analyze the association between *prakriti* (body constitution) and the prevalence of *pratishyaya* in children.

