### Inclusion Criteria

Children of either sex aged between 7 to 14 years whose parents provide written consent for enrolling their child in the study will be included if they have had the common cold with features of *pratishyaya* for 7-10 days.

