### Exclusion Criteria

Patients will be excluded if they have had the common cold for more than 10 days or if they have chronic allergic rhinitis, *dushta pratishyaya* (chronic rhinitis with complications), *raktaja pratishyaya* (a type of rhinitis with dominance of the blood element), *sannipataja pratishyaya* (rhinitis with involvement of all 3 elements), or infectious diseases such as tuberculosis. Patients will also be excluded if they have a cleft palate, a deviated nasal septum, or nasal polyps, or if they are hypersensitive to the trial drug or any of its ingredients.

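### The prevalence of pratishyaya, and its association with prakriti, cannot be estimated from a sample in which every child has the disease

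*Protocol article*

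**What the plan says.** The Secondary Objectives section states two aims. The first opens "There are 2 secondary objectives: first, to study the prevalence of" *pratishyaya* and goes on to "its origin, and its causative factors, such as viruses, bacteria, or allergies". The second reads "second, to analyze the association between *prakriti* (body constitution) and the prevalence of *pratishyaya* in children". The Methods paragraph of the abstract repeats the second aim, saying that the association between *prakriti* and "the prevalence of *pratishyaya* in children was analyzed as a secondary outcome".

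The design sections describe a population made up only of cases:

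- **Aim:** "We aim to study the efficacy of polyherbal steam inhalation versus *dhoopana* in children with *pratishyaya".
- **Inclusion Criteria:** children aged 7 to 14 years "will be included if they have had the common cold with features of" *pratishyaya* for 7 to 10 days.
- **Exclusion Criteria:** among others, children are left out "if they have chronic allergic rhinitis".
- **Recruitment, Trial Design and Table 2:** patients come from the hospital's outpatient and inpatient departments and from the surrounding region. After screening they are randomised to two treatments, 35 per group, 70 in all.
- **Results:** enrolment is complete, four children withdrew, and 66 are to be analysed.

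**The concern.** Prevalence is the proportion of a defined population that has a disease, so it needs a denominator that includes children without it. An association between a characteristic and prevalence needs disease status to vary across levels of that characteristic. A treatment trial that enrols only affected children provides neither.

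The practical risk lies in the reporting. What the trial can tabulate is how *prakriti* is distributed among the enrolled cases. If that table appears under an objective about prevalence, a predominance of one constitution will be read as evidence that it predisposes children to rhinitis. A constitution that is simply common among local children would give the same table.

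**Working it through.** **The plan's own figure.** The article gives no sample size or precision for the secondary objectives. Its only sample-size figure concerns the treatment comparison (α = 0.05, power 0.80, proportions 0.60 and 0.90). It reproduces with the two-sided formula without continuity correction:

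n = [1.96·√(2·0.75·0.25) + 0.842·√(0.6·0.4 + 0.9·0.1)]² / 0.30² = (1.200 + 0.483)² / 0.09 ≈ 31.5, so 32 per group, as stated.

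That figure has no bearing on the present point, which is about what can be identified and not about numbers.

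**Inputs from the document.** 70 enrolled, all with the disease; 66 to be analysed, all with the disease; unaffected children described: none.

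**Step 1: prevalence.** Prevalence = cases / (cases + non-cases). In this sample it is 70 / (70 + 0) = 100%, or 66 / (66 + 0) = 100%. The inclusion criteria fix this value, so it carries no information about children in general.

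**Step 2: association with prakriti.** For any *prakriti* k, the proportion diseased is 100% among children with k and 100% among children without k. The within-sample prevalence ratio is 1 by construction. The odds ratio is undefined, because both non-case cells are zero.

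**Step 3: what is missing.** Let p be the share of cases with *prakriti* k, which the trial can estimate, and q its share among unaffected children, which the trial does not observe. Then

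OR = [p / (1 − p)] / [q / (1 − q)].

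Take p = 0.50 for illustration. The values of q are assumptions, chosen to show the range:

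| Assumed q | q / (1 − q) | OR |
|---|---|---|
| 0.25 | 0.333 | 1 / 0.333 = 3.0 |
| 0.50 | 1.000 | 1 / 1.000 = 1.0 |
| 0.70 | 2.333 | 1 / 2.333 = 0.43 |

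The same observed 50% is compatible with higher risk, no difference, or lower risk. More cases would sharpen p but say nothing about q. The prevalence ratio has the same form, with q replaced by the share among all children in the population, which is also not observed.

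**Step 4: what can be estimated.** A share among enrolled cases is estimable. Its approximate 95% half-width is 1.96·√[p(1 − p)/n]:

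| Share p | n = 70 | n = 66 |
|---|---|---|
| 0.10 | 7.0 points | 7.2 points |
| 0.50 | 11.7 points | 12.1 points |

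A descriptive table of *prakriti* among cases is therefore feasible, with intervals of roughly ±7 to ±12 percentage points.

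**The case against.** The strongest reply is that a journal article condenses the full protocol and that an analysis plan may exist. That would excuse an unreported method, but the difficulty here is that the stated objective conflicts with the stated design. No analysis of 70 affected children yields a prevalence or a *prakriti*–prevalence association. Only data on unaffected children or on the source population could do so, and none are described; every participant accounted for is one of the 35 + 35 treated patients. The article mentions initial screening, and the flow diagram is not available here, so a count of children screened may exist. At most it would give a proportion among those screened, not a population prevalence.

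Other parts of the reply do stand, and they limit the point.

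- **Causes.** A reader might infer that viral, bacterial or allergic causes are equally out of reach because every child has the disease. They are not. The share of each cause among cases needs no unaffected child; only a risk-factor reading would. It is true that neither the symptom score nor the cold spatula test assigns a cause, but the article mentions a case record form and baseline parameters without listing their content, so an aetiological work-up cannot be ruled out. What does limit a cause mix is eligibility: chronic allergic rhinitis is excluded, though not every allergic cause.
- **Source of patients.** A reader might infer that most children came from the hospital. The Recruitment section also names the surrounding region and gives no split. The argument does not need that fact.
- **Reach.** The primary efficacy comparison does not depend on these objectives.

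**Conclusion.** The point holds for the prevalence of *pratishyaya* and for the association of *prakriti* with that prevalence. Disease status is 70/70 (or 66/66) by inclusion, so neither quantity can be estimated, and with illustrative shares the unidentified odds ratio runs from 0.43 to 3.0 on identical trial data. The conclusion rests on one assumption: that there is no comparison group or population denominator beyond what the article describes. The 50% share in cases and the 25%, 50% and 70% shares in unaffected children are illustrative and do not come from the document.

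The point does not extend to the distribution of causes among cases, and it does not weaken the treatment comparison. It concerns a declared secondary outcome that should be restated before results are reported.

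**What to change.** 1. Remove the word prevalence from both secondary objectives and from the secondary outcome in the abstract.
2. Restate the *prakriti* objective as its distribution among enrolled cases, with 95% confidence intervals and the number of children assessed. Label it descriptive, and say that it is not evidence of susceptibility.
3. If causes were recorded, report only their distribution among enrolled cases, and note that chronic allergic rhinitis was excluded. If they were not recorded, drop that part of the objective.
4. An analysis of *prakriti* against baseline Total Nasal Symptom Score or its change is optional. As it would be added after enrolment closed, it should be marked exploratory.

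The cost is rewording, and the claims about prevalence and susceptibility are given up. Item 2 presupposes that *prakriti* was recorded, as the declared outcome implies. Item 3 depends on what the case record form contains, which the article does not show.

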### Hypothesis

The alternate hypothesis is that *dhoopana* has equivalent efficacy to polyherbal steam inhalation in reducing the signs and symptoms of *pratishyaya* in children aged 7-14 years. The null hypothesis is that *dhoopana* does not have equivalent efficacy as polyherbal steam inhalation in reducing the signs and symptoms of *pratishyaya* in children aged 7-14 years.

### Trial Design

This will be a randomized, reference, controlled, open-label equivalence clinical study. A total of 70 patients have been recruited for the study.

## Methods

### Recruitment

The patients were selected from the outpatient and inpatient departments of the Department of Kaumarabhritya (Ayurvedic pediatrics) of Mahatma Gandhi Ayurveda College, Hospital & Research Centre and from the surrounding region. After initial screening, the patients were randomized using computer-generated random numbers into 2 groups; the control group (polyherbal steam inhalation) and the intervention group (polyherbal nasal fumigation). All baseline parameters were recorded at the start of the study. Both groups underwent treatment for 7 days. All the parameters were recorded on the third, fifth, and seventh days, with a follow-up of 28 days after the treatment period. Patients were advised to drink warm water and stay away from cold and sour items. Patients were given regular counseling and reminders through calls or messages to follow the rules and regulations of the trial.

### Guidelines

This study used the Consolidated Standards of Reporting Trials (CONSORT) guidelines; Figure 1 shows a flow diagram of the study.

